### Objectives

The present randomized controlled trial (RCT) was designed to assess the effectiveness of a combination of Ayurvedic nutritional supplements and yoga protocol in reducing the incidence and severity of AMS compared to the standard acclimatization schedule (AS) at high-altitude areas in the western Himalayan region. The key secondary objectives of this study included evaluating the impact of the Ayush intervention protocol (Ayur-nutri kit + yoga) on subjective and assessment parameters, including coagulation and hemostasis activation markers, proinflammatory markers, negative emotional states (depression, anxiety, and stress), sleep quality, and overall quality of life after 120 days. Another secondary objective was assessing the safety of Ayush interventions in AMS.

## Methods

### Study Design and Setting

The study protocol has been drafted in accordance with the Standard Protocol Items: Recommendations for Interventional Trials (SPIRIT) guidelines [26]. This clinical study was an open-label, randomized, controlled parallel-group trial. High-altitude areas are classified into three stages: stage I (9000‐12,000 feet), stage II (12,000‐15,000 feet), and stage III (more than 15,000 feet) [27]. The study was conducted at stage I and II high-altitude areas in the western Himalayan region.

### Study Participants

Apparently healthy personnel of any gender aged 18‐50 years, deemed physically fit for sojourn to high-altitude areas (in the western Himalayan regions) and willing to provide written informed consent, were included in the study. The study population consisted of individuals who were sojourning at high altitude for the first time and those who resumed sojourns after a break.

Individuals with a history of underlying cardiovascular disease or a clinically significant electrocardiogram abnormality, cerebrovascular disease, pulmonary disease, neurological disease, psychiatric illness, major venous thromboembolism (deep vein thrombosis, pulmonary embolism, or cerebrovascular thrombosis), sickle-cell disease, metabolic disorders, malignancy, glaucoma; a history of pulmonary edema or severe physiological response to high altitude (such as HAPE); evidence of uncontrolled diabetes mellitus (glycated hemoglobin more than 8.0%), uncontrolled hypertension (more than 140/90 mm Hg) even after medications, abnormal hepatic function (aspartate transaminase and/or alanine transaminase more than 2 times the upper limit of normal), or abnormal renal function (serum creatinine more than 1.2 mg%); or BMI ≥30 kg/m^2^ were excluded from the study. Similarly, those with a history of any surgery within the past 6 months; transfusion of blood or any blood product within 90 days before screening; regular use of any concomitant conventional medication; a history of chain smoking, alcohol use disorder, or substance abuse; and the presence of any other clinical condition which the investigator thinks may jeopardize the safety of the study participants were not considered for the study.

### Study Intervention

The eligible participants in the Ayush group (AG) received a comprehensive Ayush-AMS protocol, which included the use of an Ayur-nutri kit and a yoga protocol, along with the existing AS, for 120 days while staying in high-altitude regions [27].

The Ayur-nutri kit contains 2 herbal products, viz, an Ayurvedic nutritional supplement, Ayush poshak yoga, and an herbal tea, Ayush CCT, developed by the Central Council for Research in Ayurvedic Sciences, Ministry of Ayush, Government of India, to address nutritional supplementation requirements and to maintain healthy well-being at high-altitude regions. The Ayush poshak yoga powder contains a diverse blend of nuts and seeds, including cashews, almonds, pistachios, walnuts, pumpkin seeds, and cucumber seeds. It also contains herbs such as *W. somnifera* (L.) Dunal, *P. longum* L., *T. cordifolia* (Willd.) Miers ex Hook.f, *P. nigrum* L.*, Z. officinale* Roscoe., *Foeniculum vulgare* Mill., renowned for their nutritional and therapeutic benefits (Table 1). The Ayush CCT is a novel herbal tea that combines the heritage of traditional tea with a blend of herbal ingredients, including *T. arjuna* (Roxb.). Wight & Arn, saffron, cardamom, and cinnamon that can promote cardiovascular health, overall well-being, and healthy circulation (Table 1). Ayush CCT was made into an infusion by dipping one Ayush CCT tea bag in 125 mL of hot water for 5 minutes, allowing for an appropriate steeping time, and then used warm. Ayush poshak yoga was given in a dose of 25 g twice daily (morning and evening, 1 h before meals), along with 125 mL of Ayush CCT.

**Table 1. T1:** Details of ingredients of Ayush poshak yoga and Ayush CCT^a^.

Ayur-nutri kit and ingredients (botanical/English name)	Part used
Ayush poshak yoga	
*Anacardium occidentale* L. (Cashew nut)	Kernel
*Prunus amygdalus* Stokes (Almond)	Kernel
*Pistacia vera* L. (Pistachio)	Kernel
*Juglans regia* L. (Walnut)	Cotyledons
*Papaver somniferum* L.	Seed
*Chlorophytum borivilianum* Santap & R.R.Frn	Tuberous root
*Cucumis melo* L.	Seed
*Cucumis sativus* L.	Seed
*Citrullus vulgaris* Schrad.	Seed
*Cucumis melo* var. *utilissimus* Dutt & Fueller	Seed
*Zingiber officinale* Rosc	Rhizome
*Piper longum* L.	Fruit
*Piper nigrum* L.	Fruit
*Withania somnifera* (L.) Dunal.	Root
*Foeniculum vulgare* Mill.	Fruit
*Tinospora cordifolia* (Willd.) Miers	Stem
Sugar candy	
Excipients, preservatives, flavoring agents (approved)	
Ayush CCT	
*Camellia sinensis* (L.) O.Kuntze	Leaf
*Elettaria cardamomum* Maton	Seed
*Cinnamomum verum* Breyn	Stem bark
*Crocus sativus* L. (Saffron)	Style and stigma
*Terminalia arjuna* (Roxb.) Wight & Am	Stem bark

a CCT: cardiac care tea.

The yoga protocol (High-Altitude Illness Prevention Protocol of Yoga) has been tailor-made for high altitude by the Central Council for Yoga & Naturopathy, Ministry of Ayush, Government of India. The participants performed the yoga protocol under the supervision of a qualified yoga instructor. It involved sessions beginning with breathing exercises, moving onward to performing Asanas in standing posture (05 Asanas), followed by Asanas in supine (05), prone (02), and sitting postures (02). The yoga session concluded with a sequence of Pranayama and meditation or breathing exercises, totaling approximately 60 minutes each day. The yoga schedule followed an alternating pattern throughout the 120 days (Table 2). Incorporating diverse asanas within varying postures, strategically arranged in specific patterns, ensured that each sequence effectively addressed certain aspects, such as the targeted engagement of distinct muscle groups and nurturing mental well-being.

**Table 2. T2:** Details of yoga protocol (High-Altitude Illness Prevention Protocol of Yoga).

Type of yoga	Yoga practices (alternate day schedule)		Rounds	Duration^a^ (min)
	Day 1	Day 2		
Breathing exercises	Hands stretch breathing	Hands stretch breathing	—^b^	10 min
	Hands in and out breathing	Hands in and out breathing	9	
	Yogic breathing	Yogic breathing	9	
	Ankle stretch breathing	Ankle stretch breathing	9	
	*Kapalabhati kriya*	*Kapalabhati kriya*	9	
	Yogic breathing	Yogic breathing	3	
Asanas: standing	*Surya namaskar*	*Surya namaskar*	4	6 min
	*Ardha kati chakrasana*	*Trikonasana*	1	10 min
	*Padahasthasana*	*Parshvakonasana*	1	
	*Ardhachakrasana*	*Vrikshasana*	1	
	*Trikonasana*	*Veerabhadrasana*	1	
Asanas: supine	*Shavasana*—quick relaxation technique	*Shavasana*—quick relaxation technique	1	5 min
	*Uttanapadasana*	*Pawanamuktasana*	1	5 min
	*Sarvangasana*	*Suptapadangushtasana*		
	*Matsyasana*	*Viparaitakarni*		
Asanas: prone	*Bhujangasana*	*Dhanurasana*	1	4 min
	*Shalabhasana*	*Makarasana*		
Asanas: sitting	*Shashankasana*	*Ardhamatsyendrasana*	1	4 min
	*Ustrasana*	*Gomukhasana*		
Pranayama	*Nadishuddi*	*Nadishuddi*	9	6 min
	*Bhramari*	*Bhramari*	9	
Meditation or relaxation	*Om* meditation or guided meditation	*Om* meditation or guided meditation	1	10 min
	*Shavasana*	*Shavasana*	1	

a Total duration: 60 min.

b Not applicable.

The participants in the control group (CG) followed the existing AS for high altitude. The research team, comprising a medical expert, an Ayurveda practitioner, and a yoga instructor, administered the Ayush interventions at the study sites throughout the study. The participants were monitored at frequent intervals at both study sites.

Ayush CCT was provided by the Indian Medicines Pharmaceutical Corporation Limited, India, and Ayush poshak yoga by MARC Laboratories Ltd, India.

### Discontinuation of the Study Interventions

If any participant developed adverse effects, such as gastrointestinal symptoms, allergic reactions, or changes in biochemical assessment parameters, the administration of the Ayur-nutri kit was temporarily halted, and the participant was closely monitored. If symptoms recurred after reintroducing the nutritional supplements, the participant was withdrawn from the study after assessing the causality of adverse event (AE) or adverse drug reaction. All such events were recorded and reported in the AE or adverse drug reaction reporting format.

### Compliance With the Study Interventions

All participants in the AG group were provided with an information leaflet containing instructions for the use (dose, frequency, and time of administration) and storage of the Ayur-nutri kit. The participants were also issued a compliance form during the baseline visit and subsequent follow-up visits to self-report their consistent or irregular use of Ayush interventions in the Ayur-nutri kit and to record any missed doses, along with remarks for missing doses, which enabled the assessment of adherence to the dosing pattern as per the study protocol. During each follow-up visit, the participants were asked to return the used, unused, or partially used sachets of the Ayur-nutri kit to the investigators to assess adherence and cross-check with the participant’s self-reported compliance form. The participants were advised to maintain an open communication channel with the research team to address any issues they faced, including missed doses, adverse effects, and general health-related queries.

Adherence to the 60-minute daily yoga protocol was systematically monitored through instructor-maintained attendance logs at each site and also from the participant’s compliance diary. Daily session attendance was recorded for every participant throughout the intervention period.

The participants who did not adhere to the study protocol, or did not have 80% or more compliance, or those who developed any study-related AEs due to which the participant preferred to withdraw from the study, or those who withdrew their voluntary consent for participation in the study, were withdrawn from the study. If participants consented to data collection during the scheduled follow-ups or at the end of the 120 days, data were collected and recorded in the case report form (CRF). The data from completed assessments, available until the withdrawal, were used for analysis.

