### Concomitant Care

The investigators monitored the participants for any concomitant treatment they received during the study period. In the event of any AEs, the use of rescue medication was permitted under the investigator’s discretion. All instances of concomitant care were carefully documented in the CRF. However, any study participant prescribed a conventional medication for a longer duration (more than 6 consecutive days) during the study period must discontinue use of the Ayush intervention during that period. This threshold distinguishes brief, incidental, or rescue medication use from sustained therapy that could potentially interact with or confound the effects of the study intervention. All such instances were documented in the CRF. If any participant developed a serious AE or a treatment-emergent AE during the study period, the participant was withdrawn from the study and given appropriate incidental care at the hospital. The government authorities and the Ethics Committee were notified within 2 working days, along with an appropriate justification.

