### Allocation Concealment

Sequentially numbered, opaque, sealed envelopes were used to ensure allocation concealment. The participant’s enrollment number was printed at the top of the envelope, and a slip indicating the participant’s allocated group was kept inside. After completing all baseline assessments, the research staff provided the sealed envelope to the eligible participant. The participant opened the envelope and was then assigned to the group as indicated on the slip inside. The opened envelope and the printed slip were attached to the participant’s CRF for record and trial monitoring.

Participants assigned to the 2 study groups were housed in separate barracks throughout the study to prevent any protocol violations and minimize the risk of contamination bias. Further, yoga sessions and supplement distribution were conducted at designated areas accessible only to the intervention group, with attendance monitored by site instructors. The CG did not receive access to these sessions or materials, reducing the likelihood of unintentional participation. Study staff members were instructed to avoid sharing intervention-related information with control-group participants.

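### As worded, outcomes recorded after a mainly Ayush-arm withdrawal trigger are left out of the analysis; this bears on day 60 and day 120 outcomes, and the effect may be zero

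*Protocol article*

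**What the plan says.** All section names refer to the protocol article.

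- **Who is withdrawn.** Compliance With the Study Interventions lists "The participants who did not adhere to the study protocol, or did not have 80% or more compliance", together with those leaving because of study-related adverse events (AEs) or withdrawn consent. They leave the study, not just the intervention.
- **How compliance is measured.** The same section describes a form on which participants "self-report their consistent or irregular use of Ayush interventions in the Ayur-nutri kit", checked against returned sachets, and for yoga: "Adherence to the 60-minute daily yoga protocol was systematically monitored through instructor-maintained attendance logs at each site". No measure is described for the acclimatization schedule that both arms follow.
- **Who can be measured.** Allocation Concealment says of the yoga sessions and supplements: "The CG did not receive access to these sessions or materials".
- **Other triggers.** Discontinuation of the Study Interventions adds one tied to the kit: "If symptoms recurred after reintroducing the nutritional supplements, the participant was withdrawn from the study". Concomitant Care adds one that can act in either arm: "If any participant developed a serious AE or a treatment-emergent AE during the study period, the participant was withdrawn from the study".
- **What happens to later data.** Compliance With the Study Interventions says: "If participants consented to data collection during the scheduled follow-ups or at the end of the 120 days, data were collected and recorded". The next sentence reads: "The data from completed assessments, available until the withdrawal, were used for analysis".
- **What happens to gaps.** Statistical Methods sets a modified intention-to-treat approach. Participants with at least one post-baseline visit have missing values imputed by LOCF.

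**The concern.** The 80% rule is a post-randomization event. Its only described measures exist in one arm, and it may be related to tolerance, motivation or health. If outcomes recorded after that event are set aside, the day 60 and day 120 comparisons no longer use everything observed on the randomized groups, and the loss falls mainly on the Ayush side. Observed values would be replaced by older ones carried forward, which can bias the comparison in either direction.

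The outcomes exposed are the biomarkers, the mood, sleep and quality-of-life questionnaires, thromboembolic events, and the liver, kidney and lipid tests used for safety. Safety deserves a mention of its own: a participant withdrawn because symptoms recurred on the kit is one whose later laboratory results a reader would want to see.

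**Working it through.** The plan gives no figure for this effect, so the check has three parts: the text, the visit schedule, and a scale calculation on assumed inputs.

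**1. Text.** Three statements follow one another in Compliance With the Study Interventions: non-compliers leave the study; with consent, later data go into the case report form (CRF); the data used run up to withdrawal. Taken together, the third leaves out what the second collects. Statistical Methods does not restore it: the modified intention-to-treat rule keeps the participant in, but LOCF supplies a value rather than bringing back a recorded one.

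**2. Schedule (Table 3).** Compliance is assessed on days 1–7, at day 10 (stage II), and at days 30, 60 and 120. The plan does not say over what period the 80% is judged. Counting one unit per day, from day 1 to the visit:

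| Judged at | 80% of days | Missed days that breach it | Compliance then | Main visits after withdrawal |
|---|---|---|---|---|
| Day 30 | 0.8 × 30 = 24 | 7 | 23/30 = 76.7% | Days 60 and 120 |
| Day 60 | 0.8 × 60 = 48 | 13 | 47/60 = 78.3% | Day 120 |
| Day 120 | 0.8 × 120 = 96 | 25 | 95/120 = 79.2% | None |

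These counts are a simplification. The kit is taken twice daily, and the plan does not say how kit and yoga adherence combine.

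For a stage I participant without early descent, Table 3 has no biomarker or questionnaire value between baseline and day 60, and no liver or kidney test between screening and day 60. If that person is withdrawn at day 30 and LOCF is applied from the last available value, the carried value is the baseline or screening value, that is, zero change, even if day 60 and day 120 values sit in the CRF. A stage II participant would carry the day 10 biomarker and questionnaire values instead.

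**3. Scale.** Inputs:
- 830 per arm, from Sample Size (722 × 1.15 = 830.3).
- *q*, the share of the Ayush arm whose recorded later values are left out: **assumed** 1–5%. This is set well below the plan's 15% attrition, which covers all causes and both arms.
- *g*, the mean absolute difference between carried-forward and actual values in those participants: **assumed** 0.1–0.5 SD.

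The shift in the arm mean is *q* times the mean *signed* difference. Positive and negative differences cancel, so |shift| ≤ *q* × *g*, and each figure below is an upper bound for its pair of inputs.

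- Participants affected: 0.01 × 830 = 8.3 to 0.05 × 830 = 41.5, about 8 to 42.
- Low corner: 0.01 × 0.1 = 0.001 SD.
- High corner: 0.05 × 0.5 = 0.025 SD.
- Standard error of the between-arm difference, all 830 per arm analysed: √(2/830) = 0.0491 SD.
- Ratios: 0.001/0.0491 = 0.02 and 0.025/0.0491 = 0.51 standard errors.

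The bound grows in proportion to *q* and *g*, so it is only as good as those two assumptions. If compliance is judged only at day 120, *q* = 0 for this trigger and the shift is 0.

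**The case against.** The strongest reply is that the sentence does not contain the word *only*. It can be read as a minimum guarantee: withdrawn participants are not deleted, and what they gave before leaving still counts. It can also be read as covering just those who declined later collection. On either reading, consented data in the CRF are used. It would be odd to collect them and then discard them, and a value in the CRF is not missing, so LOCF would have no claim on it. The article also condenses a fuller protocol that may be explicit.

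Much of this stands. Exclusion is the plain reading, not a proven fact, and the LOCF step depends on that reading. Strengths and Limitations calls the study exploratory for its secondary outcomes, and the plan gives no withdrawal rate by arm and no share consenting to later collection.

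What does not stand is that nothing needs doing. The sentence states which data entered the analysis and gives them an end point, directly after saying that later data were recorded, and it carries neither of the suggested limits. That is an analysis rule stated in the article, not a detail left to another document. A day 120-only judgement of compliance is possible, but adherence was checked at every follow-up visit, so earlier withdrawal is plausible.

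**Conclusion.** The point holds as a minor one. On its plain wording the article leaves out outcomes recorded after withdrawal, and one of the withdrawal triggers, the 80% rule, is measurable only in the Ayush arm. The risk is to the day 60 and day 120 secondary and safety-laboratory comparisons. Size and direction cannot be determined from the document, and the effect may be zero. The largest figure, 0.025 SD or about 0.5 standard errors, is an upper bound under assumed inputs, not an estimate.

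A reader might infer three stronger things that the document does not support:

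- **That the primary AMS result is biased.** AMS is scored in the first 7 days, with 4 further days at stage II, and scores given before withdrawal still count. A material effect would need withdrawal before or during that window. Compliance is assessed in days 1–7, so this cannot be ruled out, but nothing suggests it was common.
- **That withdrawal as a whole is one-sided.** Protocol non-adherence, study-related AEs, consent withdrawal and serious or treatment-emergent AEs can act in both arms. Only the 80% rule and the kit reintroduction rule are tied to the Ayush arm.
- **That recorded data were certainly discarded.** The narrower readings remain open, and the analysis was still in progress when the article was written.

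**What to change.** Replace the sentence on data used for analysis in Compliance With the Study Interventions with:

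> All outcome data recorded in the CRF, including data collected with consent after non-adherence, an AE or stopping the intervention, are analysed in the randomized arm; imputation is used only where no data were collected.

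This settles the ambiguity whichever reading was intended. The cost is a small amount of extra analysis work, feasible because Results says the analysis is in progress. No new data are needed, and none can be had: collection ended in December 2023, so the change recovers values only for withdrawn participants who consented to continued collection. The withdrawal rule itself can no longer be changed.

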### Outcome Measures

The primary outcome was the incidence of AMS, assessed using the 2018 Lake Louise Scoring System (LLSS). AMS is defined as an LLSS score of 3 or more points from the 4 rated symptoms (headache, nausea or vomiting, fatigue, and dizziness or light-headedness), including at least 1 point from headache [9]. The grading of LLSS score is mild AMS 3‐5 points, moderate AMS 6‐9 points, and severe AMS 10‐12 points [9]. The participants were assessed daily for the first 7 days at the stage I high-altitude areas using the LLSS score to record the incidence and evaluate the severity of AMS. The primary outcome will be reported as the proportion of participants who display symptoms of AMS and the proportion of participants with a score of more than 6 as per the LLSS. The participants enrolled for stage II were again assessed daily during their first 4 days at that altitude for the incidence and severity of AMS.

The secondary outcome measures included the proportion of participants who developed thromboembolic events (deep-vein thrombosis, pulmonary embolism, cerebral venous thrombosis, myocardial infarction, etc) during the study, change in the levels of markers of coagulation and hemostasis activation (total red blood cell count, hemoglobin, packed cell volume, D-dimer, lactate dehydrogenase, creatine kinase, creatine kinase-myocardial band, fibrinogen, activated partial thromboplastin time, prothrombin time), changes in the levels of proinflammatory markers (high sensitivity C-reactive protein, interleukin-6, tumor necrosis factor-α); self-reported changes in negative emotional states of depression, anxiety, and stress assessed through Depression Anxiety Stress Scale-21 item (DASS-21); change in sleep quality assessed through the Pittsburgh Sleep Quality Index (PSQI), and quality of life assessed through the 12-item short-form (SF-12) questionnaire. The secondary outcomes were evaluated on day 60 and day 120 from baseline. However, the participants enrolled for the stage II high-altitude area were also assessed on day 10 (day 4 of the AS at that altitude) and on the day of descent, in case of early descent before day 120.

Resting heart rate, systolic and diastolic blood pressure, respiratory rate, and oxygen saturation (SpO2) were also documented daily until day 7, alongside LLSS at stage I high altitude, and until day 10 in participants at stage II high altitude. These measurements were then taken on scheduled follow-up visits.

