### Statistical Methods

The categorical data will be presented as numbers (percentages) and compared between groups using the *χ*^2^ test, while within-group comparisons will be performed by using the McNemar or Cochran Q-test. Continuous data following a normal distribution will be reported as mean (SD), and between-group comparisons will be performed using an independent sample *t*-test. Within-group comparisons for normal data will be performed using a paired sample *t*-test/repeated measures ANOVA. Nonnormal data will be reported as median (first quartile, third quartile), and between-group comparisons will be conducted using the Mann-Whitney test. Within-group comparison will be done using the Wilcoxon signed-rank test or Friedman test. Baseline variables, such as age, prior altitude exposure, and hydration-related indicators, will be examined descriptively and adjusted in multivariable models where relevant. Regression analysis will be performed to study the effect of confounding variables on the incidence of AMS. The data of participants having early descent will be analyzed with censored data models. A *P* value less than .05 will be considered significant. The SPSS version 28.0 is being used for statistical analysis.

The modified intention-to-treat analysis approach will be applied to handle missing data. The missing data for all participants for whom data are available for at least one visit post-baseline will be imputed. The last observation carried forward method will be used for imputing the missing values.

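### Analysed data appear to stop at withdrawal although later data were collected, and LOCF can then enter pre-treatment values at days 60 and 120 for some outcomes

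*Protocol article*

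**What the plan says.** Compliance With the Study Interventions lists the grounds for withdrawal: not following the protocol, participants who "did not have 80% or more compliance", study-related adverse events that lead the participant to leave, and withdrawn consent. It then provides for later follow-up: "If participants consented to data collection during the scheduled follow-ups or at the end of the 120 days, data were collected" and entered in the case report form. The next sentence reads "The data from completed assessments, available until the withdrawal, were used for analysis".

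Statistical Methods names a modified intention-to-treat approach: "The missing data for all participants for whom data are available for at least one visit post-baseline will be imputed". The method is fixed: "The last observation carried forward method will be used for imputing the missing values". Early descent is handled separately: "The data of participants having early descent will be analyzed with censored data models". Outcome Measures describes, for stage II participants, an extra assessment on day 10 and "on the day of descent, in case of early descent before day 120".

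Table 3 sets the test dates. Safety Assessment names liver, kidney and lipid tests on days 60 and 120 as part of the safety evaluation. Strengths and Limitations calls the secondary outcomes exploratory.

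**The concern.** Two rules meet badly. The first appears to set aside outcomes that were observed after withdrawal. The second replaces them with the last earlier value. Where no on-treatment value of that outcome exists, the last earlier value dates from before treatment. The participant is then counted as unchanged at day 60 and day 120, although nothing was observed, or although something different was observed and is on file.

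This affects the secondary comparisons and the laboratory safety results. A pre-treatment liver or kidney result shown at day 60 says nothing about risk under the supplements, and people who stopped early for intolerance are among those concerned.

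The effect may also be unequal. Withdrawal after a failed reintroduction of the kit (Discontinuation of the Study Interventions) can arise only in the Ayush group. So can failure on kit compliance, since only that group received a form "to self-report their consistent or irregular use of Ayush interventions in the Ayur-nutri kit".

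**Working it through.** **Step 1: which value is last?** Take a participant withdrawn before day 60 with no early-descent visit and no unscheduled test. The visits on days 1 to 7 meet the condition of one post-baseline visit. Table 3 then gives this last available value:

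| Outcome | Stage I | Stage II, withdrawn before day 10 | Stage II, withdrawn from day 10 to before day 60 |
|---|---|---|---|
| Liver, kidney, lipids | screening or baseline | screening or baseline | screening or baseline |
| Blood count, coagulation, enzyme and inflammatory markers, DASS-21, PSQI, SF-12 | screening or baseline | screening or baseline | day 10 |
| Vital signs | days 1 to 7, or day 30 | days 1 to 7 | day 10 or day 30 |

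A pre-treatment entry means a change of 0 at days 60 and 120. Vital signs are not affected. A participant whose supplements were paused for a biochemical change already has an on-treatment result for that test, so the table does not apply to it.

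**Step 2: inputs for scale.** The article gives no figure for this point, so there is none to reproduce. From Sample Size: 830 participants per stage, allocated 1:1, so 830/2 = 415 per arm in stage I; and 830 per arm over both stages. Assumed, because the documents give neither: w, the fraction of an arm whose change is set to 0, and d, a true mean change shared by both arms, in SD units. The 15% attrition in Sample Size is an overall expectation. It is used here only for scale and does not bound w.

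**Step 3: equal withdrawal.** The arm mean is (1 − w) × true mean, so a true difference is multiplied by 1 − w: 0.98 at w = 2%, 0.95 at 5%, 0.85 at 15%. No false difference arises.

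**Step 4: unequal withdrawal, no true effect.** False difference (Ayush minus control) = (wC − wA) × d. The variance in an arm is (1 − w) + w(1 − w)d². The standard error is the square root of the sum of the two arm variances divided by 415, close to √(2/415) = 0.069 SD.

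| wA / wC | d = 1: false difference | z | false-positive rate, d = 1 | false-positive rate, d = 0.5 |
|---|---|---|---|---|
| 5% / 3% | −0.02 SD | −0.29 | 6.0% | 5.3% |
| 7% / 2% | −0.05 SD | −0.72 | 11.1% | 6.6% |
| 15% / 5% | −0.10 SD | −1.45 | 30.5% | 11.7% |

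For example, for 7% / 2% and d = 1 the variances are 0.93 + 0.07 × 0.93 = 0.995 and 0.98 + 0.02 × 0.98 = 1.000. The standard error is √(1.995/415) = 0.0693, and z = −0.05/0.0693 = −0.72. A simulation of 20,000 trials with a t-test at d = 1 gave 5.5%, 11.1% and 31.0% for the three rows, and 5.0% with 5% in both arms.

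**Step 5: filled safety values.** Over both stages, w = 2% to 10% would give 0.02 × 830 = 17 to 0.10 × 830 = 83 liver and kidney values per arm and visit that were never measured at that visit.

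**The case against.** The strongest reply is that the text does not compel this reading. The sentence on withdrawal does not say that only earlier data are used. It may mean that earlier data are kept, for instance for people who declined further follow-up. Statistical Methods does not expressly say that a baseline value may be carried forward. A rule applied per variable, requiring some post-baseline value of that same outcome, would leave nothing to carry and would enter no zero change. Nor does the article say that safety tables are imputed. Such details often sit in a fuller document.

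These readings are possible, but the article states none of them. What it does state is a cut-off at withdrawal, a participant-level condition for imputation, and LOCF as the method. The ambiguity lowers confidence in what will be done; it does not remove the need to settle it.

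A reader might infer that every secondary outcome reverts to baseline for early withdrawals. Table 3 and Outcome Measures do not support that: stage II, half the sample, has a day 10 reading of most of these outcomes. The Data Collection text mentions serum and questionnaires only at baseline and days 60 and 120. If that text governed, stage II would behave like stage I, but Outcome Measures and Table 3 both schedule day 10.

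The early-descent provision also narrows the point. Table 3 gives that visit all the tests concerned, and censored-data models are named for those participants. However, withdrawal without descent triggers no such visit.

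**Conclusion.** The point holds in limited form. On the plain reading, collected outcomes are left out and LOCF can put a pre-treatment value in their place, for the outcomes and withdrawal times set out in the working. This can dilute the day 60 and day 120 comparisons or, if withdrawal differs by arm, bias them.

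The size is unknown. All values of w and d are assumptions. The 30% false-positive rate needs a 10-point excess in withdrawal and a shared change of 1 SD; a 2-point excess gives 5% to 6%.

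The documents do not support two stronger inferences. One is that withdrawal was in fact unequal: some withdrawal grounds apply only to the Ayush group, but no counts by arm are given. The other is that the trial's main result is compromised: the primary outcome is scored daily in the first 7 days and is largely untouched by imputation at days 60 and 120. The affected comparisons are secondary and declared exploratory, and adverse event reporting is a separate source on safety. The change is still worth making, because it replaces filled values with data already on file.

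**What to change.** 1. Include all consented post-withdrawal assessments in the as-randomised analysis, and reword the sentence in Compliance With the Study Interventions to say so.
2. Carry no screening or baseline value forward to day 60 or day 120 for any laboratory or questionnaire outcome. Analyse the observed data, for example with a likelihood-based repeated-measures model adjusted for baseline, and keep LOCF only as a sensitivity analysis. Such a model assumes that missingness is explained by the observed data.
3. Report safety laboratory results as observed, with the number tested at each visit. Tabulate withdrawals by arm, reason and day.

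The cost is low: a little more analysis work, and fewer values in the tables. Data collection is complete, consented follow-up results should already be in the case report forms, and the article reports the analysis as still in progress.
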